**Control drug**

|                                               |                                                                                                                                                                                                                                        |
|-----------------------------------------------|----------------------------------------------------------------------------------------------------------------------------------------------------------------------------------------------------------------------------------------|
| Generic name                                  | Erythromycin Lactobionate                                                                                                                                                                                                              |
| Product name/manufacture                      | Erythrocin for Intravenous Infusion (Mylan EPD LLC)                                                                                                                                                                                    |
| Dosage form, product description, and content | 1 vial contains 500 mg (potency) of Japanese Pharmacopoeia erythromycin lactobionate, a white powder (lyophilized injection). pH 5.0-7.5 [50 mg (potency)/mL solution]                                                                 |
| Therapeutic category                          | Macrolide antibiotic preparations                                                                                                                                                                                                      |
| Indications: susceptible strains              | Secondary infections such as trauma, burns, and surgical wounds, pneumonia, diphtheria                                                                                                                                                 |
| Indications: adaptation disease               | Staphylococcus spp., Streptococcus spp., Streptococcus pneumoniae, and Diphtheria spp. sensitive to erythromycin                                                                                                                       |
| Dosage and Administration                     | The usual adult dosage of erythromycin is 600 to 1500 mg (potency) per day divided into two to three doses and administered intravenously over at least two hours each time. The dosage may be adjusted according to age and symptoms. |
| Storage conditions                            | Store at room temperature                                                                                                                                                                                                              |

|                                               |                                                                                                                                                                                           |
|-----------------------------------------------|-------------------------------------------------------------------------------------------------------------------------------------------------------------------------------------------|
| Generic name                                  | Erythromycin Stearate Tablets                                                                                                                                                             |
| Product name/manufacture                      | Erythrosine Tablets (Mylan EPD LLC)                                                                                                                                                       |
| Dosage form, product description, and content | Enteric-coated film-coated tablets containing 200 mg of Japanese Pharmacopoeia erythromycin stearate (potency) per tablet.                                                                |
| Therapeutic category                          | Macrolide antibiotic preparations                                                                                                                                                         |
| Indications: susceptible strains              | Staphylococcus spp. (susceptible to EM), Streptococcus spp., Streptococcus pneumoniae, Neisseria gonorrhoeae, Bacillus meningitidis, Diphtheria, Shigella dysenteriae, Bacillus subtilis, |

|                                 |                                                                                                                                                                                                                                                                                                                                                                                                                                                                                                                                                                                                                                                                                                                                     |
|---------------------------------|-------------------------------------------------------------------------------------------------------------------------------------------------------------------------------------------------------------------------------------------------------------------------------------------------------------------------------------------------------------------------------------------------------------------------------------------------------------------------------------------------------------------------------------------------------------------------------------------------------------------------------------------------------------------------------------------------------------------------------------|
|                                 | Bacillus pertussis, Tetanus, Gas gangrene group, Treponema syphiliticus, Chlamydia trachomatis, Mycoplasma spp.                                                                                                                                                                                                                                                                                                                                                                                                                                                                                                                                                                                                                     |
| Indications: adaptation disease | Superficial skin infections, deep skin infections, lymphatic duct and lymphadenitis, chronic pyoderma, secondary infections from trauma, burns, and surgical wounds, mastitis, osteomyelitis, pharyngolaryngitis, tonsillitis (including peritonsillitis), acute bronchitis, pneumonia, lung abscess, empyema, secondary infection from chronic respiratory tract lesions, cystitis, pyelonephritis, urethritis, gonococcal infection, Soft chancre, syphilis, venereal (inguinal) lymphogranuloma, infectious enteritis, intrauterine infection, adnexitis, dacryocystitis, malt granuloma, otitis externa, otitis media, sinusitis, pericoronitis, scarlet fever, diphtheria, pertussis, tetanus, gas gangrene, amoebic dysentery |
| Dosage and Administration       | The usual oral dosage for adults is 800 to 1,200 mg (potency) of erythromycin daily in 4 to 6 divided doses.                                                                                                                                                                                                                                                                                                                                                                                                                                                                                                                                                                                                                        |
| Storage conditions              | Store at room temperature                                                                                                                                                                                                                                                                                                                                                                                                                                                                                                                                                                                                                                                                                                           |

### 6.1.2 PREDICTED ADVERSE EFFECTS

Both the test drug and the drug used as a control (study drug) are for off-label use. Refer to the respective package inserts/interview forms for anticipated side effects.

## 6.2 PROTOCOL TREATMENT

### 6.2.1 DOSAGE AND ADMINISTRATION

The day that the study drug Zithromax 500 mg or Erythrosine 500 mg for intravenous infusion is administered is defined as the protocol treatment start date (Day 1), and protocol treatment is initiated under inpatient supervision. The full daily dose is administered unless criteria for discontinuation of protocol treatment are met.

From the time consent is obtained until the day before protocol treatment begins, ABPC infusion or ABPC/SBT infusion can be administered.

<Intervention group>

(1) Sulbacillin for intravenous injection 1.5g

Sulbacillin for intravenous infusion 1.5 g once a day, 4 times a day for a total of 14 days (Day 1 to Day 14).

Dose intravenously over 1 hour every 6 hours  $\pm$  1 hour.

(2) Zithromax 500 mg for intravenous infusion

Zithromax 500 mg for intravenous infusion is administered intravenously 500 mg once daily for a total of 4 days (Day 1 to Day 2, Day 8 to Day 9).

Dose intravenously every 24 hours  $\pm$  2 hours over 2 hours.

(3) Zithromax Tablets 250 mg

Take one 250 mg Zithromax tablet once daily (after breakfast) for a total of 10 days (Day 3 to Day 7 and Day 10 to Day 14).

If a missed dose is noticed within 4 hours of the dose time, take the dose immediately. If more than 4 hours have elapsed, do not take that dose and resume taking the next dose as usual.

## <Control group>

- (1) Sulbacillin for intravenous injection 1.5g  
Sulbacillin for intravenous infusion 1.5 g once a day, 4 times a day for a total of 14 days (Day 1 to Day 14).  
Dose intravenously over 1 hour every 6 hours  $\pm$  1 hour.
- (2) Erythrosine for intravenous infusion 500 mg  
Erythrosine for intravenous infusion 500 mg is administered intravenously 500 mg twice daily for a total of 4 days (Day 1 to Day 2, Day 8 to Day 9).  
The drug is administered intravenously every 12 hours  $\pm$  2 hours for at least 2 hours at a time.
- (3) Erythrosine Tablet 200mg  
Take one 200 mg erythrocin tablet four times a day for a total of 10 days (Day 3 to Day 7 and Day 10 to Day 14).  
If a missed dose is noticed within 2 hours of the dose time, take the dose immediately. If more than two hours have elapsed, do not take the dose that time and resume taking it as usual the next time.

---

**6.2.2 RATIONALE FOR ESTABLISHING PROTOCOL TREATMENT**

---

## <About ABPC/ST>

In particular, since pPROM under 28 weeks of gestation are expected to have a high probability of already having an intrauterine infection, different antimicrobial management (broad-spectrum penicillins or cepheems effective against common bacteria and macrolides effective against *Ureaplasma* spp.), which is not usually used for pPROM occurring at or over than 28 weeks of gestation, will be considered.

Therefore, in this study, instead of the standard treatment recommended outside of Japan (ABPC/AMPC + EM), ABPC/AMPC was replaced by the more broad-spectrum ABPC/ST, which could be administered for up to 14 days instead of 7 days. The duration of EM administration was also set to 14 days instead of 7 days. We believe that this method may have a potential effect on BPD, which could not be expected with the conventional method.

## <About EM and AZM>

In this study, we established a dosing regimen (switch therapy) for EM and AZM that consists of 2 days of intravenous infusion plus 5 days of oral administration repeated twice.

The control group was not placebo, but ABPC/ST + EM group. The current standard treatment is ABPC (intravenous infusion) for 2 days  $\Rightarrow$  AMPC (oral) for 5 days + EM (intravenous infusion) for 2 days  $\Rightarrow$  EM (oral) for 5 days in the US, EM (oral) for 10 days in the UK, and one of the above in Canada, which all include EM. In the present study, because the number of gestational weeks is earlier than the pPROM subjects in the previous RCTs, and in many cases mixed infection by common bacteria already develops in utero, we thought it appropriate to change ABPC $\Rightarrow$ AMPC to ABPC/ST (intravenous infusion) and furthermore, to increase the administration period from 7 to 14 days. For the use of EM in the control group, we chose to use a combination of intravenous and oral EM (switch therapy), in accordance with European and US guidelines. Furthermore, since the gestational age of the patients is earlier than that of the pPROM subjects in the previous RCTs and many of them already develop intrauterine infection with *Ureaplasma*, we considered it appropriate to increase the administration period from 7 days (one course) to 14 days (two courses).

In the test group, since one objective was to verify the significance of AZM over EM, the ABPC/SBT administration method was not changed, and the EM portion of the study was administered with AZM. AZM (intravenous infusion) for 2 days ⇔ AZM (oral) for 5 days. This treatment could be continued for a maximum of two courses. The reason for this is that in a previous study, when *Ureaplasma* infection was present in the uterus, 3 days of AZM (intravenous infusion) resulted in only about 40% disappearance of *Ureaplasma* in the amniotic fluid after 1 week, and in 2 cases where 2 courses of 3-day treatment were conducted, *Ureaplasma* did not disappear, but intrauterine inflammation was controlled and BPD did not occur.

---

#### 6.2.3 DOSE CHANGE

---

No changes in protocol treatment doses are allowed in this study.

---

#### 6.2.4 INTERRUPTION OR WITHDRAWAL

---

##### (1) For intravenous infusion

Administration of intravenous infusion of the test drug or control drug may be interrupted only when an adverse event or other event occurs after the start of intravenous infusion of the test drug or control drug and it is deemed necessary to interrupt the intravenous infusion of the test drug or control drug. If the intravenous infusion is interrupted, the intravenous infusion will be resumed after the patient has recovered from symptoms and the CI or SI determines that the intravenous infusion of the test or control drug can be resumed. If intravenous administration of the test or control drug is interrupted and cannot be resumed on the day of administration, and the full dose cannot be administered, it will be treated as a drug withdrawal. If it cannot be resumed on the following day, protocol treatment should be discontinued.

If an adverse event or other event occurs after the initial intravenous administration of the test or control drug and prior to the intravenous administration of the test or control drug, and it is determined that a drug withdrawal is necessary, the drug withdrawal is acceptable. Withdrawal is limited to 1 day. If withdrawal of more than 2 days is necessary, protocol treatment should be discontinued.

##### (2) For tablets

A drug withdrawal will be permitted only when an adverse event or other event occurs after initiation of the test drug or control drug and a drug withdrawal is judged to be necessary. If a drug is withdrawn, it will be resumed after symptoms have resolved and the CI or SI determines that the study drug or control drug can be resumed.

---

#### 6.2.5 PROTOCOL TREATMENT DURATION

---

The protocol treatment period is 14 days for each group; if a decision is made to terminate the pregnancy before completing the 14-day protocol treatment, the protocol treatment is discontinued at that time.

---

#### 6.2.6 CRITERIA FOR DISCONTINUATION OF PROTOCOL TREATMENT

---

If any of the following applies, protocol treatment for the subject (mother, fetus) will be discontinued to ensure the safety of the subject (mother, fetus). If protocol treatment is discontinued, consider appropriate antimicrobial therapy for each subject (mother and fetus) and switch to a different antimicrobial therapy.

After discontinuation of protocol treatment, the subject (mother and fetus) should continue to participate in the study unless "10.1 Cancellation of participation in the trial" applies, and the CI or SI should continue observation, investigation, and testing in accordance with the schedule (7.5).

1. When intrauterine infection is strongly suspected due to Lencki's diagnostic criteria or other reasons.  
Diagnostic criteria for clinical chorioamnionitis (CAM) by Lencki, et al.
  - 1) If maternal temperature is  $\geq 38.0$  degrees Celsius and at least one of the following 4 items (A to D) is observed: A. maternal tachycardia  $\geq 100$  beats/min, B. uterine tenderness, C. foul-smelling vaginal discharge or amniotic fluid, D. leukocytosis ( $\geq 15\,000/\text{mm}^3$ )
  - 2) If all of the above 4 items are observed even if the mother's body temperature is  $< 38.0$  degrees CelsiusHowever, since there is a possibility that 1) may occur due to pneumonia, pyelonephritis, appendicitis, meningitis, influenza, etc., these should be differentially diagnosed as much as possible during maternal fever.
2. When *Pseudomonas aeruginosa* or multidrug-resistant bacteria are detected in vaginal culture.
3. When adverse events occur, and it is necessary to withdraw protocol treatment for intravenous drip infusion for 2 days or more.
4. When the delivery is determined.
5. When the subject desires to discontinue protocol treatment.
6. In addition, when the attending physicians determine that it is difficult to continue the protocol treatment.

---

#### 6.2.7 PACKAGING AND LABELING

Commercially available drugs Sulbacillin 1.5g for Injection (Meiji Seika Pharma Co., Ltd.), ZITHROMAC Intravenous use (Pfizer Inc.), ZITHROMAC tablets (Pfizer Inc.), Erythrocin for Intravenous Infusion (Mylan EPD LLC), and Erythrosine Tablets (Mylan EPD LLC) will be purchased for use in the study. Water for injection, saline solution, and 5% dextrose solution necessary for drug preparation and administration will also be purchased and used for the study. Study drugs should be managed and used separately from drugs that are usually prescribed in the clinic. Details will be specified separately in the study drug administration procedures for this study.

---

#### 6.2.8 PREPARATION AND POST-PROCESSING

Dissolve 1.5 g of Sulbacillin 1.5g for Injection in 100 mL of rehydration solution and infuse intravenously over 1 hour. Use promptly after dissolution.

Dissolve ZITHROMAC Intravenous use in 4.8 mL of water for injection (concentration 100 mg/mL) and dilute to an injectable concentration of 1.0 mg/mL using an infusion solution such as 5% dextrose injection solution that has been confirmed to be free of compositional changes. When preparing a 100 mg/mL solution, do not use any solution other than water for injection, since there is no preparation data available. Use immediately after dissolution.

To prepare a 5% solution, add 10 mL of water for injection to one vial of erythrosine. The 5% solution is stable in the refrigerator for 2 weeks.

Zithromax Tablets 250 mg and Erythrosine Tablets 200 mg are oral medications in tablet form and should be removed from the PTP sheet immediately before taking. There is no special preparation required in advance.

### 6.3 MANAGEMENT METHOD

#### 6.3.1 STORAGE AND DELIVERY

Study drugs will be purchased for study purposes and stored appropriately in the pharmacy or pharmacy department of each institution. When delivered, they should be prescribed for study use and provided directly to subjects by the CI or study partner pharmacist or SI. Unused and expired medications due to missed doses will be disposed of as usual in accordance with the hospital's drug disposal procedures. Details will be specified separately in the study drug administration procedures for this study.

#### 6.3.2 DISPOSAL/RETURN

If a study drug is not used during the study period due to damage, contamination, or other defects in the study drug, the number of vials to be disposed of, serial number, expiration date, reason for disposal, and number of vials in stock after disposal should be recorded on the study drug control chart. When discarding, dispose of as medical waste in accordance with the regulations of each medical institution.

At the end of the study drug administration period, unused study drug product should not be returned or otherwise disposed of as medical waste in the same manner as for disposal.

### 6.4 CONCOMITANT MEDICATIONS

#### 6.4.1 CONCOMITANT MEDICATIONS

The following items will be entered in the electronic case report form (eCRF) when the following drugs are used on the subject (mother or fetus) (maternal) from the date consent is obtained to the end of study participation (or when study participation is canceled).

- Ritodrine hydrochloride
- Magnesium sulfate
- Betamethasone
- Antimicrobials used during exacerbations of infection after the end of the protocol treatment period

The following items will also be entered in the eCRF when an adverse fetal event occurs from the date of protocol treatment initiation to the time of pregnancy termination (or cancellation of participation in the trial) and when a drug or therapy other than the study drug is used for the adverse event.

Name of drug/therapy

route of administration

Start and end date of treatment

Reason for use (treatment)

Note that no entry is required for saline or other rehydration or dissolution solutions that are not intended for treatment.

#### 6.4.2 CONCOMITANT RESTRICTED DRUGS AND CONCOMITANT RESTRICTED TREATMENTS

The use of corticosteroids during the period of participation in the study will be permitted only for the following purposes, from the time consent is obtained until the termination of pregnancy.

- (1) Use of maternal administration to prevent the onset of RDS via fetal lung maturation when preterm delivery is anticipated.
- (2) Topical for skin, bronchus, ear, nose, throat, eye, oral cavity, anus, vagina, etc.
- (3) Use of prednisolone for treatment of complications prior to study participation.

The use of antimicrobial agents from the time consent is obtained until the start of protocol treatment will only be allowed for ABPC infusion or ABPC/SBT infusion if deemed necessary by the CI or SI.

#### **6.4.3 ANTIMICROBIAL THERAPY FOR EXACERBATIONS OF INFECTION AFTER COMPLETION OF PROTOCOL TREATMENT**

---

If an exacerbation of infection is observed after completion of protocol treatment and before termination of pregnancy, antimicrobial therapy other than macrolide therapy may be administered, as deemed appropriate by the CI or SI.

For the purposes of this study, an infection exacerbation is defined as any of the following:

- (1) WBC count or CRP level is worse than during the protocol treatment period, and the CI or SI determines that antimicrobial therapy is necessary
- (2) Vaginal culture showing *Pseudomonas aeruginosa* or multidrug-resistant bacteria

#### **6.4.4 CONCOMITANT PROHIBITED TREATMENT**

---

In the control group, the following drugs must not be used concomitantly from the time consent is obtained until the end of the protocol treatment period.

- (1) Macrolide preparations other than erythromycin
- (2) Ergotamine (ergotamine tartrate, dihydroergotamine mesylate) containing preparations [CLEAMIN®, DIGIDELGOT®, etc.]
- (3) Pimozide [Orap®].
- (4) Asunaprevir [Sunbepre®].

Basis for setting

- (1) Set for the same drug as the control drug.
- (2) - (4): These were selected because the control drugs bind to CYP3A and form a complex, which may inhibit the metabolism of these drugs.

In the study group, the following drugs may not be used concomitantly from the time consent is obtained until the end of the treatment observation period.

- (1) Macrolide preparations other than azithromycin

Basis for setting

- (1) Set because of the same drug class as the test drug control.

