| Combination Prohibited | <Intervention group>
(1) Macrolide preparations other than azithromycin
<Control group>
(1) Macrolide preparations other than erythromycin
(2) Ergotamine (ergotamine tartrate, dihydroergotamine mesylate) containing preparations [Cleamin®, Digidelgot®, etc.]
(3) Pimozide [Orap®]
(4) Asunaprevir [Sunbeptra®]             |
| Study system           | ○ Principal Investigator and Representative Institute
[name], Professor, Department of Maternal and Fetal Intensive Care Unit, Perinatal Medical Center, Jichi Medical University Hospital
○ Study Secretariat
[name], Part-time Lecturer, Department of Obstetrics and Gynecology, Jichi Medical University Hospital   |

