## **4 STUDY DESIGN**

### **4.1 STUDY DESIGN**

To compare the efficacy and safety of AZM and EM in combination with ABPC/SBT for the prevention of BPD in infants born to pregnant women with pPROM occurring at <28 weeks of

gestation, we will plan a phase II, multicenter, open-label, randomized, parallel-group study. The efficacy of AZM and EM will be evaluated by comparing the rate of events, with events defined as BPD36 of moderate or greater and infant death up to 36 weeks PMA. Safety will be evaluated by the occurrence of adverse events and side effects in mother and child.

The study is a clinical trial conducted during the hospitalization period for pregnant women admitted after the onset of pPROM and consists of a screening phase, a treatment observation phase from the date of protocol treatment initiation to termination of pregnancy, and a post-termination observation phase from termination of pregnancy to the date of discharge of the child.

The chief investigator (CI) or sub-investigator (SI) will screen and assess eligibility after obtaining consent. The CI or SI will enroll subjects in REDCap prior to the start of protocol treatment. After enrollment, eligible subjects will be assigned to the intervention or control group by stratified allocation. The screening period from obtaining consent to randomization will be a maximum of 3 days.

The CI or SI will initiate protocol treatment within 4 days of obtaining consent. The study drug Zithromax 500 mg for intravenous infusion or Erythrosine 500 mg for intravenous infusion will be administered under inpatient supervision with the start date as Day 1.

The protocol treatment period is 14 days from Day 1 to Day 14. If a decision of termination of pregnancy is made\*1 before completing the 14 days of dosing, the protocol treatment will be discontinued at that time.

From the end of protocol treatment until “date of birth”\*2, the prescribed observations, investigations, and tests are performed under inpatient supervision.

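### Section 6.4.4 ends the ban on the non-assigned macrolides at Day 14 in the erythromycin arm but at termination of pregnancy in the azithromycin arm, without a reason

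*Protocol*

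**What the plan says.** Section 6.4.4 of the protocol has one list of banned drugs per arm.

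- **EM arm (control).** Item (1) covers all macrolides except erythromycin, so it includes AZM. Items (2)-(4) are ergotamine products, pimozide and asunaprevir. None may be used "concomitantly from the time consent is obtained until the end of the protocol treatment period".
- **AZM arm (study group).** The only item covers all macrolides except azithromycin, so it includes EM. It may not be used "concomitantly from the time consent is obtained until the end of the treatment observation period".

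The stated basis for the macrolide item is "Set for the same drug as the control drug" in the EM arm and "Set because of the same drug class as the test drug control" in the AZM arm. Items (2)-(4) have their own basis, inhibition of CYP3A metabolism by the control drug.

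Section 4.1 defines both periods. On the first it says: "The protocol treatment period is 14 days from Day 1 to Day 14". Section 6.2.5 agrees: "The protocol treatment period is 14 days for each group". The second is "a treatment observation phase from the date of protocol treatment initiation to termination of pregnancy".

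The synopsis (section 1.1) lists the same bans, for example "Macrolide preparations other than erythromycin" for the control group, with no time window.

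**The concern.** AZM against EM is the only contrast that the trial tests, and treatment is open-label. The rule that keeps each arm's macrolide out of the other arm should therefore be the same on both sides. As written, it lapses earlier in the EM arm, and the drug then no longer barred there is the test drug.

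What is at stake is consistency. Section 14.1 forms the per protocol set (PPS) by removing, from the full analysis set (FAS), subjects with deviations that concern protocol treatment or prohibited drugs. If the prohibited-drug rule has a different end date in each arm, the same conduct counts as a deviation in one arm and not in the other.

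**Working it through.** The protocol gives no figure on this point, so the check sets the texts side by side.

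**Step 1: the end of each ban.**

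| | EM arm | AZM arm |
|---|---|---|
| Non-assigned macrolide of interest | AZM | EM |
| Ban starts (6.4.4) | Consent | Consent |
| Ban ends (6.4.4) | With the protocol treatment period | With the treatment observation period |
| Calendar meaning | Day 14 (4.1, 6.2.5) | Termination of pregnancy (4.1) |

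Section 4.1 speaks of a treatment observation phase and 6.4.4 of a period. Section 7.5.1 (6) and (7) show that these are the same thing: they list the treatment observation period and next the observation period after termination of pregnancy.

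**Step 2: is a reason given?** The two notes on the macrolide items say why the drugs were chosen. Neither addresses when the ban ends. The CYP3A note would justify a limit tied to EM dosing, but it covers only items (2)-(4).

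**Step 3: what other sections already close.** Section 6.4.3 applies without naming an arm. For an infection exacerbation after protocol treatment and before termination of pregnancy, it allows only non-macrolide antimicrobials. Section 6.4.1 describes apparently the same therapy as given once the protocol treatment period is over. Read together, they block AZM for a defined exacerbation after Day 14 in both arms.

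**Step 4: what is left.** An EM-arm woman, after Day 14 and before delivery, receives AZM for a reason other than a defined exacerbation. Under 6.4.4 this is not a prohibited-drug deviation. EM given to an AZM-arm woman on the same day is one.

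**Step 5: length of the window.** For delivery on Day D, the AZM-arm ban outlasts the EM-arm ban by max(0, D − 14) days. Taking visit days from Table 1.3-1 as example delivery days:

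- D = 15: 15 − 14 = 1 day
- D = 22: 22 − 14 = 8 days
- D = 36: 36 − 14 = 22 days
- D = 50: 50 − 14 = 36 days

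For a woman who delivers by Day 14 the difference is zero. Section 5.2.2 gives a median of 2 weeks, which I read as the time from rupture to delivery. Day 1 falls after rupture, and up to 4 days after consent. On that figure about half the women or more might deliver by roughly Day 14. This is only a rough guide, because women with imminent delivery are excluded and those enrolled may stay pregnant longer. The documents do not fix the share.

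**The case against.** The strongest reply is that the gap hardly matters. Worsening infection is the obvious reason to give more antimicrobials, and 6.4.3 closes that route equally in both arms. The documents name no other indication for AZM after enrolment and give no frequency. This stands, and it is why the point is minor.

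It can also be said that 6.4.4 concerns concomitant use, meaning use alongside study drug. That does not remove the difference: both arms' texts use the word, yet the AZM-arm text runs on to termination of pregnancy. The mismatch may well be a wording slip, but sites apply the text as written.

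A reader might infer more in two places.

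- **Early stoppers.** Section 6.2.6 tells sites to switch antimicrobials after discontinuation and repeats no macrolide limit, so AZM might seem open to any EM-arm woman who stops early. The documents do not support this well. Before Day 14, 6.2.5 says that it is the treatment that stops, which favours a ban running to Day 14. After Day 14, 6.4.1 suggests that 6.4.3 covers exacerbations whether or not all 14 days were given. What is left is again the other-indication case.
- **Dilution of the treatment effect.** One could assume that some EM-arm women cross over to AZM and compute a loss of power. The documents give no crossover rate, and nothing in them establishes that late AZM confers the full AZM-arm risk. Such a figure would rest on assumption alone.

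**Conclusion.** The inconsistency is real and stands on the face of 6.4.4. The ban on non-assigned macrolides ends at Day 14 in one arm and at termination of pregnancy in the other, and the stated bases do not explain it. The consequence is limited to how the prohibited-drug criterion for the PPS works: it differs by arm on the tested contrast, for women still pregnant after Day 14 and for uses outside 6.4.3.

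No frequency, power loss or bias is claimed. The primary analysis uses the FAS, and its definition in 14.1 does not refer to prohibited drugs. The missing time window in the synopsis is ordinary summarising and not a second fault; it only means that the synopsis cannot settle the matter.

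The conclusion rests on two readings: that the treatment observation period in 6.4.4 is the phase defined in 4.1, and that 6.4.3 applies from the end of the protocol treatment period. If 6.4.3 were held to apply only after 14 completed days of treatment, the gap would be somewhat wider. Severity: minor.

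**What to change.** In 6.4.4, end the ban on non-assigned macrolides (item (1) in each list) at termination of pregnancy in both arms. This matches the span of 6.4.3. Keep the protocol-treatment-period limit for items (2)-(4) in the EM arm, where the CYP3A reason supports it.

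Ending both bans at Day 14 would also remove the asymmetry, but it would leave each arm open to the other's macrolide before delivery, so the later common end point is better.

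The cost is a change of protocol wording and its committee review. No extra patients, visits or procedures are needed.
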